## SUMMARY

This study aims to evaluate the effects on the prevention of overweight of three approaches that are currently being applied in Dutch preventive Youth Health Care (YHC) to parents of infants and toddlers: (a) 'Usual care', i.e. common advices regarding nutrition and playing of the infant and toddler; (b) 'BOFT+', i.e. a training of YHC-nurses regarding their skills to advice parents regarding parenting; and (c) the 'Healthy toddler', i.e. a specific advice to parents of toddlers at age 18 months and 24 months regarding nutritional habits, playing habits and watching TV, supported by a written advice generated by Internet.

Forty-five Youth Health Care (YHC) teams of circa 10 regional YHC providers will participate in this study with net 1.500 children. The 45 teams will be assigned at random to (a) continue 'Usual care' (15 teams), or (b) to participate in the training for nurses regarding parenting skills (i.e. 15 'BOFT+' teams), or to (c) YHC-teams that will apply the 'Healthy toddler' face-to-face consultation at age 18-months regarding nutritional habits, playing habits and watching TV, supported by an Internet generated, tailored written advice (15 teams). Informed consent to participate in this study will be obtained from the parents during a regular home visit by member of the YHC-team circa 2 weeks after birth; follow-up of the parents and their children is till the child is 36 months old.

According to the current YHC Overweight prevention protocol ('Overbruggingsplan') YHC-teams, in order to contribute to the prevention of overweight in childhood should promote 1) breastfeeding, 2) outdoor exercise, activity and play, 3) having breakfast daily, 4) few soft drinks and 5) less TV time (in Dutch: 'B-BOFT'-behaviors).

(a)

'Care as usual' consists of common advices regarding nutrition and playing of the infant and toddler, and the above-mentioned 'B-BOFT' behaviors are part of such advices that are given according to the Product Description YHC, i.e. the regular scheme of YHC visits, e.g. through oral information and generic information leaflets.

(b)

The 'BOFT+' intervention is also based on this approach. However, the YHC-nurses in the 'BOFT+' teams will be trained how to provide parents with parenting skills necessary to act according to the recommended behaviors (e.g. only few TV time). In 'BOFT+', the YHC-nurses will have more knowledge and skills to augment usual care with explicit guidelines on childrearing. These guidelines are simple and encompass principles of stimulus control and modeling. YHC-workers will therefore be able to educate parents in how to set concrete boundaries for their children and how to create preconditions to make the child behave positively. The YHC-nurses will know how to advice parents regarding structuring time and space, how to implement rules and habits, how to be unambiguous and consistent and how to set clear boundaries. The nurses will be trained how to help parents controlling stimuli, and how unwanted behavior can be avoided. Parenting skills based on operant conditioning

will be incorporated in the training of professionals. Enlarging parenting skills is thought to be a precondition in order to change child-rearing styles.

(c)

The 'Healthy toddler' intervention is also based on the YHC-Overweight prevention protocol and has a focus on the promotion of parenting competence by face-to-face counseling, using a counseling style called 'motivational interviewing', strengthened by a dedicated E-health module. The 4 recommended behaviors, daily exercise/outdoor playing, family breakfast daily, few sugar sweetened drinks, minimal TV time ('BOFT'), and associated parenting skills/attitudes will be assessed by the E-health module, prior to face-to-face counseling and result in a tailored advice, subsequently discussed during face-to-face counseling by a trained YHC-professional using motivational interviewing techniques. The E-health module includes a written reminder of useful information at approximately 1 month after the YHC-visit. The 'Healthy toddler' intervention will be provided twice to the parents/toddlers: at the age of 18 months and 24 months.

The study questions are:

1. Effect evaluation

What are the effects of (1) the 'BOFT+' intervention, applied from birth onwards and (2) the 'Healthy toddler' intervention, applied when the child becomes a toddler, in terms of (a) improvement of energy balance-related behaviors, i.e. daily outdoor playing, daily family breakfast, few sugar sweetened drinks per day, and limited TV time per day, (b) in terms of optimal parenting practices/style, and (c) in terms of measures of body fatness at the population level, at follow-up at age circa 36 months?

2. Process evaluation

What is the adherence of parents and YHC professionals to the distinct elements of the 'BOFT+' intervention and the 'Healthy toddler' intervention, how do they appreciate these elements, how often and to whom are these elements applied?

3. Cost-effectiveness evaluation

What is the ratio between costs and effects in terms of improvement of the four behaviors and potential future reduction in the prevalence of overweight of the 'BOFT+' and the 'Healthy toddler' intervention compared to a control group receiving usual care?

We will explore differences in effects and process characteristics for subgroups of socially disadvantaged and non-Dutch children.

## 1. INTRODUCTION AND RATIONALE

In the Netherlands, preventive Youth Health Care (YHC - Jeugdgezondheidszorg) is committed to counsel parents regarding parenting competence, and to promote healthy development and growth for all children (Basistakenpakket Jeugdgezondheidszorg, 2002). These YHC-tasks are of utmost importance nowadays, as the prevalence of overweight and obesity among children has at least doubled in the past 25 years, especially in socially disadvantaged and specific ethnic subgroups (Fredriks 2005; Whitlock 2005).

Distinct elements of the Product Description YHC (Basistakenpakket JGZ) are being elaborated into national YHC consensus statements and eventually into evidence-based protocols (Standaarden Jeugdgezondheidszorg). Currently, consensus regarding overweight prevention has been reached through the YHC-Overweight detection protocol (Signaleringsprotocol overgewicht; Bulk-Bunschoten 2005) and the YHC-Overweight prevention protocol (Overbruggingsplan overgewicht; Hirasing 2005).

The YHC-Overweight prevention protocol consists of a strategy for primary prevention of overweight (i.e. promotion of healthy energy balance-related behaviors in the whole child population) and a strategy for secondary prevention of overweight (i.e. detection of children with established overweight and intensive counseling of these children and their parents).

In this protocol the effectiveness of two specific interventions regarding primary prevention of overweight and obesity will be evaluated in a clustered randomized trial. The two new interventions, 'BOFT+' and the 'Healthy toddler', are fully based on the YHC Overweight-prevention-protocol with a focus on promotion of parenting competence. They are easily applied in the YHC setting, but differ in content and complexity.

The control condition in the study is 'care as usual', i.e. care according to the Product Description YHC, i.e. the regular scheme of YHC visits during which general information regarding nutrition, playing and exercise is provided, e.g. through oral information and generic information leaflets, acknowledging the knowledge of the YHC-Overweight Prevention Protocol that states that breastfeeding is preferred over bottle feeding and that parents should promote healthy nutrition and exercise (Basistakenpakket Jeugdgezondheidszorg, 2002; Hirasing et al., 2005).

In intervention arm (a) of the study, the BOFT+ intervention aims at implementing healthy life-style habits continuously, from early age on (from birth on) to three years of age. The nurses of the YHC-teams that participate in the BOFT+ intervention will be trained in how parents can be supported in general parenting skills. This training is based on results of a previous study on determinants of behavior that is related to overweight in young children (Boere-Boonekamp, 2005; ZonMw Grant # 50-50140-98). The approach focuses on training the YHC-nurses how to help parents with the transition to a new phase in life, namely that of a young parent; people are more receptive to changes during such transitional moments. In

this arm the education and counseling of parents will not only focus on eating habits and exercise, but also on childrearing issues, by using elements of the learning theory and enlarging parental sensitivity together with high expectations concerning the possibility of self-control of the child (the so called authoritative parenting style). YHC nurses will apply the new approach during each YHC-contact with parent(s) in the preschool period. Examples of the techniques that will be used are: modeling, stimulus control, and intermittent confirmation.

In intervention arm (b) of the study, the 'Healthy toddler' intervention will be provided by YHC professionals to parents 2 times: (1) at the age of approximately 18 months, and (2) at the age of approximately 24 months. The nurses that participate in the 'Healthy toddler' intervention will apply motivational interviewing techniques during the face-to-face consultation and address child-rearing issues related to healthy habits (Hirasing et al., 2005). The focus is on 4 priority behaviors ('BOFT'): (1) Promotion of daily exercise and outdoor playing time; (2) Having a family breakfast daily; (3) Lessening intake of sugar sweetened drinks; (4) Limitation of TV time (in Dutch 'BOFT': Buiten spelen, Ontbijten, Frisdrankgebruik ontmoedigen, TV kijken). These behaviors and associated attitudes are assessed by an E-health module resulting in a tailored advice, subsequently discussed during face-to-face counseling. The E-health module includes a reminder circa 1 month after face-to-face counseling. The module was developed and implemented in ZonMw project # 4010.0033, named 'The start of healthy living'. The combination of prior on-line assessment, tailored advice, face-to-face counseling, and an E-health 'booster' is a promising combination (Mangunkusumo, 2006).

### **Context analysis and related studies**

Given the epidemic increase of relative overweight and obesity in childhood (Whitlock 2005), all involved parties are fully aware of the necessity of effective prevention strategies, are therefore willing to contribute to the study, and eager to learn and implement the results.

January 2007, parties that collaborate in the current study, started a ZonMw cluster-randomized trial to evaluate the YHC-Overweight detection protocol (Bulk-Bunschoten 2005) in combination with the YHC-Overweight prevention protocol (Hirasing 2005), at the child age of 5 years, i.e. school-going children, with a focus on selection of children with overweight, i.e. secondary prevention.

From the field of YHC several requests emerged to evaluate, in addition, the Overweight-prevention protocol with the focus on primary (not secondary) prevention of overweight by YHC-nurses and physicians among preschool children. The argument is that primary prevention is necessary, and probably effective, in very young children who are in the process of developing their habitual energy balance-related behaviors; once these behaviors have been established it is considered to take more effort to induce change (Hirasing 2005).

In the past months, parties of the current study have developed an educational course for YHC-nurses and -physicians based on the previous study on determinants of behavior related to overweight in young children (Boere-Boonekamp 2005; ZonMw Grant # 50-50140-98 and Fonds OGZ). A pilot of the first part of this course is planned for October 10, 2007. After adaptation, this part of the course can be used in the 'BOFT+' research arm of the project at hand. Recently, an application for development of a comparable course for teachers of preschool and nursery facilities was submitted to ZonMw as well (continuation of the Fonds OGZ project).

The primary prevention element of the YHC-Overweight prevention protocol, to be evaluated in this study, has broad support among policy makers and managers as well as among the YHC professionals, including the YHC-nurses.

## **2. OBJECTIVES**

In this study we will evaluate the effects of 2 distinct primary prevention strategies regarding overweight in preventive Youth Health Care (YHC) for preschool children (Jeugdgezondheidszorg 0-4 jarigen): (a) the 'BOFT+' intervention with - as primary starting point - a focus on child rearing issues that are relevant for the development of behaviors related to overweight, starting at birth and using elements of learning theory, stimulus control and modeling (based on ZonMw project # 50-50140-98); (b) The 'Healthy toddler' intervention with - as primary starting point - a focus on behaviors related to overweight using E-health in combination with face-to-face counseling and motivational interviewing for parents of young toddlers (18-24 months) (based on ZonMw project # 4010.0033). Both are based on the broadly accepted YHC-Overweight-prevention-protocol, saying that five behaviors should be promoted: breast feeding, daily exercise/outdoor playing, family breakfast daily, few sugar sweetened drinks, minimal TV time (so-called 'B-BOFT' behaviors). The control condition in the study implies 'usual care' according to the Product Description YHC with general information regarding nutrition, playing and exercise, e.g. through oral information and generic information leaflets.

Study questions:

### **Effect evaluation**

1. What are the effects of (a) the 'BOFT+' intervention applied from birth onwards and (b) the 'Healthy toddler' intervention applied when the child becomes a toddler, in terms of improvement of energy balance-related behaviors, i.e. daily outdoor playing, daily family breakfast, few sugar sweetened drinks per day, and limited TV time per day (in Dutch 'BOFT' behaviors), in terms of optimal parenting practices/style, and in terms of measures of body fatness at the population level, at follow-up at age circa 36 months?

**Process evaluation**

2. What is the adherence of parents and YHC professionals to the distinct elements of the 'BOFT+' intervention and the 'Healthy toddler' intervention, how do they appreciate these elements, how often and to whom are these elements applied?

**Cost-effectiveness evaluation**

3. What is the ratio between costs and effects in terms of improvement of the four behaviors and potential future reduction in the prevalence of overweight of the 'BOFT+'- and the 'Healthy toddler' interventions compared to a control group receiving usual care?

We will explore differences in effects and process characteristics (e.g. adherence) for subgroups socially disadvantaged and non-Dutch children.

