The 'Healthy toddler' intervention consists of an E-health module with tailored advice to parents regarding the 'BOFT' behaviors of their toddler and related child rearing practices, which is combined with face-to-face counseling in the setting of regular YHC at the child age of circa 18 months for the first time and at child age of circa 24 months for the second time. The E-health module is offered prior to both visits, and is repeated, as a reminder, a month after both visits. The face-to-face counseling will address specific issues raised by the E-health module, including questions that the parents may have. As proposed by the YHC-Overweight-prevention-protocol YHC-professionals will make use of motivational interviewing techniques in the two counseling sessions. As specific YHC-visiting schemes vary by region in the Netherlands, some variation will be allowed regarding age of application.

The study is designed as a cluster-randomized trial (c-RCT) with two intervention conditions (see above) and a control condition ('usual care'), with inclusion shortly after child birth, repeated measurements prior to and during the interventions, and a follow-up measurement at age 36 months, which is circa 12 months after the last intervention contact with the parents around the age of 24 months old in both intervention groups. The YHC-team (Consultatiebureau-team) is the unit of randomization in order to avoid contamination between the intervention condition and the control group condition within teams (Campbell et al., 2004).

Circa ten regional services providing Youth Health Care for preschool children (in Dutch: Jeugdgezondheidszorg 0-4 jaar, or Ouder- en Kindzorg) from metropolitan and non-metropolitan areas, to be selected in an open procedure, will participate in the study with a total of 45 Youth Health Care teams (Consultatiebureau-teams). Within each service, YHC-teams will randomly be assigned to either one of the two intervention groups or the control group. The last follow-up measurement in the study that we propose now will take place at the age of circa 36 months, during a regular visit to the YHC center in combination with a self-report questionnaire. A process and cost-effectiveness evaluation will accompany the effect evaluation. When the study is successful, follow-up projects with continuation of the interventions and/or follow-up measurements at older age will be proposed at ZonMw or other funding organizations in the future.

Figure 1.

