**Numbers of parents/children included in the study**

A total of 45 YHC-teams of circa ten regional services providing Youth Health Care, will participate in the study. We assume, on average, 15 toddlers per age group per month per YHC-team to be scheduled for a regular visit at a certain age (i.e. 2 weeks after birth at the start of the inclusion procedure). In the course of an inclusion period of maximally 12 months in the project, the 45 participating YHC-teams together will have invited a total of 3.000 parents/toddlers in the study (two intervention groups and one control group).

Taking into account informed consent by 50% and dropout between baseline and follow-up of 30%, we expect complete data from a total of 1.050 parents/toddlers at follow-up, equally divided over the control group and the two intervention groups.

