### **Cost-effectiveness analyses:**

Costs and effects will be evaluated for the purpose of a cost-effectiveness analysis. Potential future reduction in the prevalence of overweight will be estimated together with an estimation of costs saved (Haby et al., 2006).

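### The cost-effectiveness question sets each programme only against usual care, so its two ratios do not show which of the three arms is the best option

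*Protocol*

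**What the plan says.** The Summary opens with "This study aims to evaluate the effects on the prevention of overweight of three approaches". Section 3 (Study Design) says that within each service "YHC-teams will randomly be assigned to either one of the two intervention groups or the control group", so a team delivers one condition only and there is no combined arm. Section 1 says of the two new programmes: "They are easily applied in the YHC setting, but differ in content and complexity".

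Study question 3 appears twice with the same comparator. Section 2 (Cost-effectiveness evaluation) asks for the ratio between costs and effects "of the 'BOFT+'- and the 'Healthy toddler' interventions compared to a control group receiving usual care". The Summary asks for the same ratio "of the 'BOFT+' and the 'Healthy toddler' intervention compared to a control group receiving usual care".

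Section 6 (Measures regarding the Cost-effectiveness evaluation) lists the cost items for both interventions: extra contact time, training and other programme costs. Section 7 (Cost-effectiveness analyses) says only "Costs and effects will be evaluated for the purpose of a cost-effectiveness analysis", followed by an estimate of the future reduction in overweight and of costs saved. Neither section compares the two programmes with each other, orders the options or names a threshold. The power considerations in section 4 likewise treat only an intervention against control.

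**The concern.** When several alternatives compete, the ratio that bears on choosing a more costly one is its extra cost over its extra effect relative to the next cheaper option still in contention. A ratio against usual care credits the dearer programme with effect that the cheaper one may already deliver. A programme can then look acceptable although it is dominated (the other costs less and achieves more), or although its last increment of effect is very expensive.

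The comparator is written into the study question itself, so an analysis that follows the question to the letter would deliver two ratios against usual care and stop there. A service reading those results to choose between the programmes would lack the comparison it needs.

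**Working it through.** The protocol states no cost, ratio or threshold, so there is no figure of its own to reproduce. The check is algebraic, with **assumed** values per child. Call the programmes X and Y; the labels can be swapped between BOFT+ and Healthy toddler.

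**Formulas.** ΔC and ΔE are cost and effect relative to usual care, and λ is the threshold per unit of effect.
- Ratio against usual care: ΔC/ΔE
- Ratio between programmes: (ΔC_Y − ΔC_X)/(ΔE_Y − ΔE_X)
- Net benefit: λ·ΔE − ΔC

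**1. Base illustration.** X: ΔC = 20, ΔE = 0.04. Y: ΔC = 60, ΔE = 0.06.
- X against usual care: 20/0.04 = 500
- Y against usual care: 60/0.06 = 1000
- Y against X: (60 − 20)/(0.06 − 0.04) = 2000

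| λ | Net benefit X | Net benefit Y | Better |
|---|---|---|---|
| 1500 | 60 − 20 = 40 | 90 − 60 = 30 | X |
| 2000 | 80 − 20 = 60 | 120 − 60 = 60 | equal |
| 2500 | 100 − 20 = 80 | 150 − 60 = 90 | Y |

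Between 1000 and 2000 both programmes pass against usual care, but X is the better choice. Above 2000, Y is better although its ratio against usual care is twice that of X.

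**2. Range over the effect of Y, costs held fixed.**
- ΔE_Y = 0.05: 60/0.05 = 1200 against usual care; 40/0.01 = 4000 against X
- ΔE_Y = 0.08: 60/0.08 = 750 against usual care; 40/0.04 = 1000 against X

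**3. The same two ratios, different decisions.** Keep X as above (500) and hold Y at 1000, but let its effect differ.
- ΔE_Y = 0.05, so ΔC_Y = 50: Y against X = (50 − 20)/0.01 = 3000
- ΔE_Y = 0.06, so ΔC_Y = 60: Y against X = 2000

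At λ = 2500, net benefit of X is 80. Y gives 125 − 50 = 75 in the first case and 90 in the second. The better option changes while the two ratios stay at 500 and 1000, so the ratios alone do not settle the ranking.

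**4. Dominance.** X: ΔC = 40, ΔE = 0.04, ratio 1000. Y: ΔC = 35, ΔE = 0.05, ratio 700. X costs more and achieves less, so it is dominated, yet at a threshold above 1000 it passes against usual care.

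**5. Extended dominance.** X: ΔC = 20, ΔE = 0.02, ratio 1000. Y: ΔC = 60, ΔE = 0.08, ratio 750. Y against X: 40/0.06 = 667, below the 1000 paid to reach X. X should drop out, which its own ratio against usual care does not show.

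**6. Precision of the added contrast.** From section 4: 1,050/3 = 350 children per arm, cluster size 1,050/45 = 23.3, intra-class correlation 0.10, equal standard deviations. The design effect is 1 + 22.33 × 0.10 = 3.233. The standard error of a difference in means between any two arms is SD × √(2 × 3.233/350) = 0.136 SD. The effect contrast between the programmes is therefore, in absolute terms, as precise as either contrast with control.

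**The case against.** The strongest reply is that naming a comparator does not forbid other comparisons. Question 3 does not restrict itself to usual care in so many words, sets no threshold and has no rule that the lowest ratio wins. If incremental costs and effects are reported for each arm, the contrast between programmes follows by subtraction. Question 3 also matches the effect question and the power section, which set each intervention against control. The programmes start at different ages, and nothing says that practice must adopt only one. All of this stands. It limits the point to how the results are specified and read; nothing is lost in the design. It does not remove the point, because no section commits to the comparison and the comparator is fixed in the question itself, not left open for an analysis plan.

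Several stronger readings are tempting but unsupported.
- A reader might infer that the stated ratios cannot inform a choice at all, or will reverse it. They do answer whether each programme is worth having instead of usual care, and the comparison can be recovered from the underlying costs and effects.
- A reader might infer that training costs will be inflated by spreading them over enrolled children only. Section 6 counts training as a cost but fixes no denominator. The size of any such error is also unclear: "15 toddlers per age group per month per YHC-team" gives 15 × 12 = 180 a year, while 3,000 invited over at most 12 months gives 3,000/45 = 66.7 per team. Against 1,500/45 = 33.3 enrolled, the factor would be 5.4 or 2.0.
- Bootstrap method, acceptability curves and the handling of near-zero effects are ordinary analysis-plan detail. Their absence from the protocol is no fault.

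**Conclusion.** The point holds in a limited form. As worded, question 3 yields two comparisons with usual care and no comparison among all three options, although the trial randomises teams to three exclusive conditions. In the assumed base example, the figure that decides between the programmes (2000) is twice the larger ratio against usual care (1000). Over the range of effects shown with costs fixed, it runs from 1000 to 4000. These values show that the problem can arise. They do not show that it will, and its frequency cannot be computed from the protocol. The conclusion assumes that a service would treat the programmes as alternatives, as the trial does. It is worth correcting because the correction is standard and nearly free, not because the planned comparisons are wrong.

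**What to change.** In study question 3 (Summary and section 2) and in the cost-effectiveness paragraph of section 7, keep the comparisons with usual care and add a full incremental analysis of the three arms:
- order the arms by mean cost;
- exclude dominated and extendedly dominated options;
- report each remaining option's incremental ratio, or its net benefit, against the next cheaper remaining option;
- give the uncertainty with allowance for clustering by team.

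The costs of both interventions and the effects in all arms are already to be collected, so no new data are needed. The price is a little more analysis and a between-programme ratio that may be unstable if the two effects are similar. Reporting net benefit alongside avoids dividing by that small difference.
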